### Intervention

#### Rational for acupuncture protocol

Having screened for a range of acupuncture points for tinnitus through a systematic review of records of ancient books, as well as the standardized acupuncture protocol devised by acupuncture experts in China, we formed the acupuncture protocol for this trial. Three basic points used for each subject are *Tinggong* (SI19), *Ermen* (SJ21) and *Tinghui* (GB2) (Figure 2). These acupoints are on the Small Intestinal Meridian of Hand - *Taiyang*, *Sanjiao* Meridian of Hand - *Shaoyang* and the Gallbladder Meridian of Foot - *Shaoyang*. The three meridians bypass the ear. Because there is a theory stating that therapeutic effects might be elicited by placing needles on acupuncture meridians relating to specific organs, appropriate meridians and acupoints which are in close relationship with the ear are chosen as basic treatment for tinnitus in this study. Also, as has been mentioned in traditional Chinese theory, tinnitus can be classified as three subtypes according to tinnitus-related syndromes: retention of phlegm-heat, hyperactivity of Liver-*yang*, and deficiency of Kidney-*yin*. The first two are excess syndromes while the later belongs to deficiency. Then appropriate secondary acupoints are also added as follows (Figure 3):

**Figure 2 Fig2:**
[figure not shown]
**Location of basic acupoints - three basic points are used for each patient, and include**
***Tinggong***
**(SI19),**
***Ermen***
**(SJ21) and**
***Tinghui***
**(GB2).**

**Figure 3 Fig3:**
[figure not shown]
**Location of secondary acupoints - according to syndrome differentiation of tinnitus, the appropriate secondary points could be chosen:**
***Fenglong***
**(ST40) and**
***Laogong***
**(PC8) for retention of phlegm-heat,**
***Taichong***
**(LR3) and**
***Qiuxu***
**(GB40) for hyperactivity of Liver-**
***yang***
**, and**
***Guanyuan***
**(BL26) and**
***Taixi***
**(KI13) for deficiency of Kidney-**
***yin***
**.**

For subtypes of retention of phlegm-heat: *Fenglong* (ST40), *Laogong* (PC8)For subtypes of hyperactivity of Liver-*yang*: *Taichong* (LR3), *Qiuxu* (GB40)For subtypes of deficiency of Kidney-*yin*: *Guanyuan* (BL26), *Taixi* (KI13)

Participants in either the manipulation group or the non-manipulation group are all diagnosed by the methods of interrogation, inspection, auscultation and palpation. Then, the syndromes of the patients are differentiated in accordance with the clinical materials acquired through the diagnostic methods to classify them into either the syndrome of retention of phlegm-heat, the syndrome of hyperactivity of Liver-*yang*, or the syndrome of deficiency of Kidney-*yin*. Based on the diagnostic pattern of TCM, an appropriate acupuncture plan for each patient is selected individually. We also believe that this selective treatment could be performed more effectively and we hope to explore this in our study.

### Acupuncture administration

All candidates go through a standardized interview and undergo a temporal bone computed tomography (CT) scan, audiological testing of hearing thresholds, minimal masking levels, and loudness discomfort levels. Participants will also be asked to complete the Tinnitus Severity Index Questionnaire (a standard questionnaire with 13 items for quality of life in patients suffering tinnitus), Tinnitus Loudness Questionnaire, the Hospital Anxiety and Depression Scale (HANDS) at the screening visit and at 4, 8 and 16 weeks after randomization. The patients in both the manipulation group and the non-manipulation group are blinded as to which treatment method they would receive. For both groups, treatment consists of five daily sessions of thirty minutes each time for four consecutive weeks.

Acupuncture will be performed by an acupuncturist who has more than ten years experience and has obtained an acupuncture license (Chinese medicine practitioner license), which is licensed by the Ministry of Health of the People’s Republic of China). In order to make the patients comfortable and relaxed during treatment, a constant humidity and a temperature of 20 to 25°C is necessary. Subjects will be advised to assume a supine position on the bed. As has been mentioned above, three basic points and three to four secondary acupoints are selected for each patient according to syndrome differentiation. When the acupoint sites have been located and disinfected with 75% alcohol cotton, a sterile disposable stainless needle of 0.3 mm diameter and 25 mm in length (Suzhou Hualun Medical Appliance Co., Ltd, Jiangsu, China) is inserted gently into the SI19, GB2, SJ21, PC8 and LR3 points separately for a depth of about 0.25 to 0.5 *cun*. For ST40, GB40, BL26 and KI13, a needle with the diameter of 0.3 mm and a length of 40 mm is used with the approximate puncture depth of 0.5 to 1 *cun*. It is advisable to retain the needles for 10 to 20 minutes for the subtypes of deficiency of Kidney-*yin*, while this is not necessary for the other two subtypes with excess syndromes. For the whole treatment, the insertion and withdrawal of the needle is at a constant speed.

For the manipulation group, patients are to be acupunctured with some genuine manipulations by lifting, thrusting, and twirling the needle to generate needle sensation, known as *De Qi* (described above). When *De Qi* occurs, the internal compound sensation of soreness, numbness, distension, dull pain, coldness, warmth, heaviness, and radiation at and around puncture points may be felt. Also, the acupuncturists may also feel the sensation of sinking, stagnancy, tightness and astringency. In non-manipulation group, the acupuncturist inserts the needles without using any acupuncture techniques. Patients receive one treatment session daily for five consecutive days, and the total treatment course lasts for four weeks.

### Assessment of acupuncture sensation ‘*De Qi*’

The Chinese version of the ‘modified’ Massachusetts General Hospital Acupuncture Sensation Scale (C-MMASS) is used to record the patients’ sensations of *De Qi* quantitatively. The C-MMASS was established on the basis of MASS. In C-MMAS, the terms have been translated into precise Chinese, but one description, ‘sharp pain’, was removed from the scale. The validity and reliability of the scale have been examined by exploratory study [15]. The descriptor in C-MMASS includes soreness, aching, deep pressure, heaviness, fullness/distension, tingling, numbness, dull pain, warmth, cold, throbbing, and there is one supplementary row at the end for subjects to describe perceptions in their own words. Each of the elements is presented on a 10-cm bar to indicate the degree of needle sensation from ‘none’, ‘mild’, ‘moderate’ to ‘severe’. Subjects are asked to quantify their sensations at each acupoint immediately after each treatment by rating their intensities on the numerical bar. If the participants have any sensations not given in the scale, they could describe them at the end of the scale. Then, for each subject, the total *De Qi* scores of the 20 sessions will be calculated together for final statistical analysis.

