## Abstract

**Background:**

Acupuncture has been used in China to treat tinnitus for a long time. There is debate as to whether or not *De Qi* is a key factor in achieving the efficacy of acupuncture. However, there is no sufficient evidence obtained from randomized controlled trials to confirm the role of *De Qi* in the treatment of acupuncture for tinnitus. This study aims to identify the effect of *De Qi* for patients who receive acupuncture to alleviate tinnitus by a prospective, double-blind, randomized, sham-controlled trial.

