### Statistical analysis

We conducted a pilot study, in which the similar outcome measurements were used, to determine the sample size prospectively. In this pilot study, the two methods of manipulation and non-manipulation were about 70 and 50% effective respectively when the patients underwent acupuncture 5 times a week for 4 weeks. Based on the population rates of the two groups, the following formula is used to estimate sample size [16]:

Calculations are performed c 5% significance level. In the formula, α = 0.05, Z_0.05_  = 1.96, β = 0.10, Z_0.10_  = 1.282; n_1_, n_2_ represents the sample size of each group respectively and π_1_ = 0.50, π_2_ = 0.70, π_c_ = (π_1_ + π_2_)/2 = 0.60. Thus as a result, an estimated 146 patients per group should be recruited when allowing for a 15% withdrawal rate.

Statistical analysis will be performed using the statistical software package SPSS 19.0 for windows (SPSS Inc, Chicago, IL, USA). Firstly, the baseline characteristics of the two groups, such as age, weight, duration of tinnitus, THI and VAS scores, will be analyzed by an unpaired *t*-test or paired t tests. Then, the second step is to compare the efficacy of *De Qi* or not in the treatment of tinnitus. The average intensity of *De Qi*, the total number of *De Qi* acupoints of all the treatment sessions, the scores of THI and VAS will be tested for normal distribution. If the data follow normal distribution, a two-sample (independent) *t*-test will be used. The data that are not conforming to the normal distribution will undergo Wilcoxon testing. A level of *P*-value less than 0.05 will be considered statistically significant.

Furthermore, the intention-to-treat analysis (ITT) and per-protocol (PP) analysis should be conducted as two principles to test whether the result of this trial is credible. Any cause of withdrawal or loss to follow-up should be clarified. Qualified statisticians will perform the statistical analysis in a blinded manner.

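### The article names conflicting De Qi summaries for the final analysis, and two of them, the total and the count, rise with attendance and needle count as well as with sensation

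*Protocol article*

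**What the plan says.** In the protocol article, the section on assessing De Qi sets the unit of measurement: "Subjects are asked to quantify their sensations at each acupoint immediately after each treatment". It then sets the summary: for each subject, the total De Qi "scores of the 20 sessions will be calculated together for final statistical analysis".

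The Statistical analysis section names other variables. The first is "The average intensity of" De Qi. The second is the total number of De Qi "acupoints of all the treatment sessions, the scores of THI and VAS will be tested for normal distribution". All of these are compared between groups by an independent t-test or, if not normal, a Wilcoxon test. The step is introduced with the words "the second step is to compare the efficacy of" De Qi or its absence.

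On the number of needles, the Acupuncture administration section says that "three basic points and three to four secondary acupoints are selected for each patient according to syndrome differentiation". The section on the rationale for the acupuncture protocol gives the same three basic points but lists only two secondary points for each of the three syndrome subtypes.

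**The concern.** Both sections describe what enters the final analysis, yet a total is not an average, and neither is a count. As written, three De Qi summaries are available, and the choice among them could be made after the data are seen.

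The summaries are also not interchangeable. A sum or count of ratings taken per point and per session mixes how strongly De Qi was felt with how many ratings were made. Missed sessions are foreseen: the section on withdrawal covers patients who do not want the assigned treatment or cannot fully take part. Attendance could plausibly differ by arm, since only one arm receives manipulation meant to provoke soreness, numbness and dull pain. If it does differ, the total and the count can create or hide a De Qi difference between arms.

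Wording is at stake too. Both arms are needled, and manipulation is only intended to elicit De Qi. An arm difference in De Qi shows whether the manipulation worked as intended. An arm difference in THI or VAS shows the effect of manipulating the needles. Neither is, by itself, a comparison of De Qi with no De Qi.

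**Working it through.** **Plan's own figures.** Sessions: 5 per week × 4 weeks = 20, as the article says. The sample size also reproduces. With rates of 0.50 and 0.70, two-sided 5% and 90% power, the pooled two-proportion formula gives 124 per group, and 124/0.85 = 146. It is not in dispute here and does not change.

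**Number of ratings per patient.** Ratings = points × sessions attended. For illustration, assume one score per point at a constant intensity of 3 on the 10-cm bar.

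| Points | Sessions | Ratings | Total | Mean per point per attended session |
|---|---|---|---|---|
| 6 | 20 | 120 | 360 | 3 |
| 7 | 20 | 140 | 420 | 3 |
| 6 | 10 | 60 | 180 | 3 |
| 7 | 10 | 70 | 210 | 3 |

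- Attendance: 180/360 = 0.50, so half the sessions gives half the total at the same sensation.
- Needle count within the Acupuncture administration section (3 + 3 = 6 to 3 + 4 = 7): 420/360 = 7/6 = 1.17, about 17% more.
- A count of De Qi acupoints scales in the same two ways.

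**The average depends on its denominator.** For 6 points and 10 sessions, dividing the total by the 20 planned sessions gives 180/20 = 9, against 360/20 = 18 with full attendance. Dividing by the sessions attended gives 180/10 = 18 in both cases. An average over ratings actually made is free of the attendance effect; an average over planned sessions is only the total rescaled.

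**Effect on the between-arm test.** A simulation gave both arms the same distribution of sensation per needle (124 per arm, 2,000 runs) and varied attendance only. The inputs are assumptions, not figures from the article: mean intensity 4, SD 1.5, 5 to 7 points per patient in both arms, 60% of points De Qi-positive, and the attendance rates shown. Proportion of runs in which the 5% t-test rejected:

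| Attendance by arm | Total | Average per rating | Count |
|---|---|---|---|
| 90% vs 90% | 5% | 5% | 5% |
| 90% vs 85% | 20% | 4% | 71% |
| 95% vs 85% | 57% | 5% | 100% |

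With equal attendance all three measures hold their level, although needle count varies between patients. So variation in needle count that is alike in both arms is noise, not bias. With unequal attendance only the total and the count go wrong. The figures for the count are probably high, because every patient was given the same 60% probability; real variation between patients would lower them.

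**The case against.** The strongest defence is that the Statistical analysis section lists average intensity first, and an average over ratings made does not carry the artefact. On that reading the section on assessing De Qi is loosely worded and the analysis is nearly right already. This stands in part: it would be wrong to say that the De Qi analysis consists only of sums. It does not remove the conflict, because the total is expressly sent to the final analysis, the count remains a named test variable, and the average has no stated denominator.

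Several stronger readings are tempting and are not supported.

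- A reader might infer that the trial leaves its own question unanswered because no analysis links a patient's De Qi to THI or VAS. The Background states the question as strong versus weak stimulation, and the randomised THI and VAS comparison answers that. A De Qi-to-THI model would be an optional observational analysis, which a condensed article may leave to the analysis plan.
- A reader might infer that De Qi is treated as an efficacy outcome because it is listed beside THI and VAS. The section on measurements of tinnitus assigns efficacy to THI and VAS.
- A reader might compare patients with 6 or 7 points against patients with 5 and find 20% to 40%. That compares two contradictory sections, not patients within one plan.
- A reader might infer that syndrome mix biases the arm comparison. Syndrome is diagnosed in the same way in both arms and allocation is randomised 1:1, so it is balanced in expectation.
- A reader might apply the 15% withdrawal allowance to the 20 sessions. Its timing is not stated, and withdrawal during the 12-week follow-up cannot alter a score that is complete at week 4.

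**Conclusion.** The point holds as a conflict between two sections, with a defect in two of the three summaries named. The total and the count depend on sessions attended (half the sessions, half the score) and on points needled (7 against 6, about 17%). Bias in the arm comparison arises only if attendance differs by arm. The article gives no figures on that, so the simulated rejection rates show direction and possible scale, not a forecast. They also assume that sensation does not drift over sessions and is unrelated to who attends.

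The consequence is confined to the De Qi measures, which serve as a check of the manipulation, and to how the conclusions are worded. The THI and VAS comparison and the sample size of 146 per group are untouched. The correction is nearly free and should be made before the data are analysed.

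**What to change.** - Use one definition in both sections: mean C-MMASS intensity per needled point per attended session.
- Replace the count of De Qi acupoints by the proportion of needled points with De Qi, over the sessions attended.
- Report the between-arm difference in these measures as a check of the manipulation.
- Word the efficacy conclusion from THI and VAS as the effect of manipulation versus no manipulation.
- Reconcile the number of points per patient: three basic plus two listed per subtype in the rationale section, against three basic plus three to four secondary in the Acupuncture administration section. Which is intended is for the investigators to settle.

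The cost is a change of analysis wording. The ratings per point and per session are already planned, so no further data are needed.

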### Measurements of tinnitus

The efficacy of acupuncture treatment for tinnitus is assessed in terms of the severity and loudness of tinnitus. Tinnitus Handicap Inventory (THI) and a 10-cm Visual Analog Scale (VAS) are used. Patients complete the THI and VAS before the treatment and every four weeks during the following period. The 25-item THI consists of three scales: a functional subscale, a catastrophic response subscale and an emotional subscale. Before and after the acupuncture treatment, the participants are asked to report their tinnitus on the THI Questionnaire with ‘Yes’ (4 points), ‘Sometimes’ (2 points) or ‘No’ (0 points). Based on the total THI score, each patient’s tinnitus severity could be categorized into ‘no handicap’ (0 to 16), ‘mild handicap’ (18 to 36), ‘moderate handicap’ (38 to 56) and ‘severe handicap’ (58 to 100).

### Patient safety

Before randomization, patients will be asked to undergo routine tests of blood, urine and stool; an electrocardiogram (ECG), liver function, hepatitis serology, HIV serum antibody assay, blood glucose, and kidney functions are needed to exclude any related serious illness. The results of these tests will allow the assessment of risks associated with catgut implantation at acupoints. If any adverse effect occurs during the trial, patients will be treated as soon as possible.

### Quality control

All acupuncturists are required to receive special training, including the technique for puncture and the way to deal with adverse events. The acupuncturists should also learn how to use the randomization method in order to communicate with patients and to keep them blind to the treatment throughout the trial. Only those who have completed the required training and have passed all necessary examinations will be recruited for this trial. In order to maintain quality of this trial, all outcome assessments will be blinded. In addition, all researchers must understand the purpose and design of this trial. Audits will be conducted regularly on compliance with standard operation procedures every week. Report of audits should be presented to the chief monitor. If patients withdraw from the trial either in the treatment period or in the follow-up phase, the reason should be clarified and the rate should be statistically analyzed.

### Statistical analysis

We conducted a pilot study, in which the similar outcome measurements were used, to determine the sample size prospectively. In this pilot study, the two methods of manipulation and non-manipulation were about 70 and 50% effective respectively when the patients underwent acupuncture 5 times a week for 4 weeks. Based on the population rates of the two groups, the following formula is used to estimate sample size [16]:

Calculations are performed c 5% significance level. In the formula, α = 0.05, Z_0.05_  = 1.96, β = 0.10, Z_0.10_  = 1.282; n_1_, n_2_ represents the sample size of each group respectively and π_1_ = 0.50, π_2_ = 0.70, π_c_ = (π_1_ + π_2_)/2 = 0.60. Thus as a result, an estimated 146 patients per group should be recruited when allowing for a 15% withdrawal rate.

Statistical analysis will be performed using the statistical software package SPSS 19.0 for windows (SPSS Inc, Chicago, IL, USA). Firstly, the baseline characteristics of the two groups, such as age, weight, duration of tinnitus, THI and VAS scores, will be analyzed by an unpaired *t*-test or paired t tests. Then, the second step is to compare the efficacy of *De Qi* or not in the treatment of tinnitus. The average intensity of *De Qi*, the total number of *De Qi* acupoints of all the treatment sessions, the scores of THI and VAS will be tested for normal distribution. If the data follow normal distribution, a two-sample (independent) *t*-test will be used. The data that are not conforming to the normal distribution will undergo Wilcoxon testing. A level of *P*-value less than 0.05 will be considered statistically significant.

Furthermore, the intention-to-treat analysis (ITT) and per-protocol (PP) analysis should be conducted as two principles to test whether the result of this trial is credible. Any cause of withdrawal or loss to follow-up should be clarified. Qualified statisticians will perform the statistical analysis in a blinded manner.

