### Recruitment and randomization procedures

The participants will be recruited through advertisements in local newspapers, hospital websites, and television. Printed recruitment posters will also be posted in the hospital and the university campus. Then, the participants will be randomly assigned to either the manipulation or the non-manipulation group with an assignment ratio of 1:1 according to the random number of allocation sequence generated by computer (using SPSS 19.0 statistical software package, IBM, Chicago, IL, USA). The random allocation numbers are sealed separately in opaque envelopes separately. After the participants have picked-up one of the envelopes, their random numbers and corresponding randomization information, such as the participant’s name in a pinyin format and gender, will be recorded in a random allocation table in duplicate and sealed in an opaque container respectively. The container will not be opened until blinding has ceased. A well-trained acupuncture practitioner, who has practiced for more than ten years, performs the intervention according to the assignment. Also, the acupuncturist does not participate in any of the subsequent evaluation phases. Investigators, including the study physicians and the analyzing statistician, are blinded to the manipulation group assignment.

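### THI and VAS are compared by a t-test or Wilcoxon test chosen on a normality test, with no adjustment for the baseline scores collected, and a paired t-test is named for two independent groups

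*Protocol article*

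**What the plan says.** The Statistical analysis section of the protocol article sets out two steps.

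- **Baseline.** "Firstly, the baseline characteristics of the two groups, such as age, weight, duration of tinnitus, THI and VAS scores" are to be analysed by an unpaired t-test "or paired t tests".
- **Efficacy.** Together with two De Qi measures, "the scores of THI and VAS will be tested for normal distribution". Normally distributed data go to an independent two-sample t-test. For the rest, "The data that are not conforming to the normal distribution will undergo Wilcoxon testing". The significance threshold is 0.05.

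No covariate, change score, ANCOVA or repeated-measures model is named. Under Measurements of tinnitus, however, the baseline values are collected: "Patients complete the THI and VAS before the treatment and every four weeks during the following period". Allocation is simple two-arm randomisation "with an assignment ratio of 1:1" (Recruitment and randomization procedures), so the arms are independent and nothing in the design creates pairs.

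**The concern.** Three features of the stated analysis are weak.

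1. **Baseline is not used in the efficacy test.** The entry criteria require subjective tinnitus but set no minimum severity, so patients may enter anywhere on the THI scale. A patient's pre-treatment score is then likely to predict the later score, and an unadjusted comparison leaves that predictable variation in the error term. A chance difference in baseline THI also carries into the result. The first step might reveal such a difference, but the second step states no way to deal with it.
2. **The data select the test.** The t-test compares means and the rank test compares distributions by rank. With a normality test as the switch, the quantity being estimated is unknown until the data are in, and it could differ between THI and VAS or between visits.
3. **Baseline testing.** Significance tests of baseline differences say nothing useful when allocation is random, and a paired t-test cannot compare two independent groups.

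At stake are the width of the confidence interval, the power to detect a modest effect, and a clear statement of what is being estimated.

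**Working it through.** **The plan's own figure first.** Inputs from Statistical analysis: two-sided α = 0.05 (z = 1.96), β = 0.10 (z = 1.282), rates 0.50 and 0.70, mean rate 0.60, 15% withdrawal.

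n = [1.96·√(2·0.60·0.40) + 1.282·√(0.50·0.50 + 0.70·0.30)]² / 0.20² = 124.04, taken as 124 per arm. Then 124/0.85 = 145.9, or 146. The stated 146 per group reproduces and is not affected by this point. The calculations below use 124 evaluable patients per arm.

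**Assumed inputs.** The article gives no SD for THI or VAS and no baseline to follow-up correlation r. I take r = 0.5 to 0.7, equal SDs at baseline and follow-up, and a linear relation. Results are in SD units.

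**Variance of the arm comparison, relative to the follow-up score alone**

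- Follow-up score: 1
- Change score: 2(1 − r)
- ANCOVA: 1 − r²

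ANCOVA therefore saves r² against follow-up scores. Against change scores the ratio is (1 − r²)/[2(1 − r)] = (1 + r)/2, a saving of (1 − r)/2.

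| r | Saving vs follow-up | Equivalent n per arm, 124/(1 − r²) | Saving vs change | Equivalent n per arm, 124·2/(1 + r) |
|---|---|---|---|---|
| 0.5 | 25% | 165 | 25% | 165 |
| 0.6 | 36% | 194 | 20% | 155 |
| 0.7 | 49% | 243 | 15% | 146 |

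**Power at an assumed difference of 0.30 SD** (124 per arm, two-sided 0.05, noncentral t with noncentrality 0.30/√(2v/124), where v is the relative variance above)

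| r | Follow-up score | Change score | ANCOVA |
|---|---|---|---|
| 0.5 | 65% | 65% | 78% |
| 0.7 | 65% | 86% | 91% |

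**Power at a larger effect.** The sample size rests on a pilot in which "the two methods of manipulation and non-manipulation were about 70 and 50% effective respectively". If being effective means crossing a cut on a normally distributed score (an assumption), the shift is Φ⁻¹(0.70) − Φ⁻¹(0.50) = 0.524 SD. The unadjusted test of follow-up scores then has about 98% power, so adjustment mainly narrows the interval. Against follow-up scores the width is multiplied by √(1 − r²), which is 0.87 at r = 0.5 and 0.71 at r = 0.7.

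**Chance imbalance.** Suppose the arms differ at baseline by 1.96 standard errors and there is no treatment effect. Given that, the test statistic for follow-up scores has mean 1.96r and variance 1 − r². The false-positive rate is about 13% at r = 0.5, 16% at r = 0.6 and 21% at r = 0.7, instead of 5%. For change scores, the correlation with baseline has absolute size √((1 − r)/2), which is 0.50 at r = 0.5 and 0.39 at r = 0.7. The same calculation gives about 13% and 10%, so protection is better at the higher correlation but incomplete.

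**Baseline tests.** Five characteristics are listed. If they were independent, 1 − 0.95⁵ = 23% is the chance of at least one significant difference under correct randomisation.

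**Does the normality switch distort the error rate?** In a simulation of the two-stage rule (Shapiro-Wilk, then t or Wilcoxon, 124 per arm, 4,000 runs, no effect), the type I error was 0.0495 with normal data and 0.050 with skewed gamma data. It does not.

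**The case against.** - **The efficacy test is valid.** A reader might infer that an unadjusted or normality-selected test inflates the false-positive rate. The documents do not support that. Under 1:1 randomisation the unadjusted two-sample test holds its level over all allocations, and the simulation shows no inflation from the switch. The imbalance figures are conditional on an unlucky allocation. This objection stands in full.
- **The scores may be changes from baseline.** A reader might infer that baseline is ignored altogether. The article does not settle this. If changes are tested, baseline is used, and at r = 0.7 the gain from ANCOVA is modest. This stands, and it is why both sets of figures are given.
- **The sizes rest on assumptions.** Neither r nor the 0.30 SD effect is in the article. Nor does the absence of a severity threshold show that baseline dominates the later variance: at r = 0.5 to 0.7 baseline explains 25% to 49% of it, less than half. This also stands.
- **Covariates belong in a statistical analysis plan.** Visit modelling and extra covariates can be left there. But the article itself names the tests, the rule for choosing between them and the threshold, so the point concerns what it states.
- **The paired t-test is probably a misplaced reference to before-after comparisons within arms.** That is plausible, and the efficacy step does name an independent test, so no between-arm efficacy result rests on pairing. The sentence as printed still applies it to baseline characteristics of the two groups and needs correcting. Baseline P-values trigger no stated decision, so they mislead the reader without harming the efficacy inference.

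**Conclusion.** The point holds as a loss of efficiency and clarity, together with one wrongly named test. It is not a failure of validity, and the sample size of 146 per group is unaffected.

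The size of the gain depends on what the scores are and on r. For r = 0.5 to 0.7, the saving in variance rises from 25% to 49% if follow-up values are tested and falls from 25% to 15% if changes are tested. In power this matters most for modest effects such as the assumed 0.30 SD. Near 0.52 SD the trial is already well powered and the benefit is mainly a tighter interval. I am confident of the direction and of the wording error, and less so of the size, because the article gives neither r nor an SD.

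**What to change.** - Make ANCOVA of THI (and of VAS), with arm and baseline score as terms, the prespecified efficacy analysis. Report the adjusted mean difference with its 95% confidence interval.
- Do not let a normality test choose the analysis. Keep the rank-sum test as a sensitivity analysis.
- Describe baseline characteristics by arm without P-values, and delete the reference to paired t-tests.
- Optional: a repeated-measures model over the four-weekly visits, and syndrome subtype as a covariate.

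The cost is analysis wording only. The baseline scores are already collected, the sample size does not change, and SPSS, the package named in the article, fits these models.
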